### Sample size calculation

Given that there are no meta-analyses available for internet interventions of family centered parenting and adolescent programs, studies reporting face-to-face parenting and adolescent interventions and internet interventions directed at health behavior change were used to inform power calculations [50]. A meta-analysis of psychological interventions to improve outcomes in children and adolescents with T1D reported a moderate effect of family therapy on child/adolescent psychological distress (ES = .46) and HbA1c (ES = .41) [51]. A meta-analysis of internet interventions aiming to promote adolescent health related behaviors showed moderate effects (ES = .33) for interventions grounded in Cognitive Behavioral Theory or Theory of Planned Behavior [44]. Therefore a medium effect size is expected on the primary adolescent mental health outcome measure, as measured by the CDI and the RCMAS-S, between the two groups across the three assessment points. To power the study at the 80% level, based on an alpha level of .05, with an estimated medium effect size (.40) and with two groups over three assessment points, 64 complete responses will be required. Given that self-help online intervention studies often report high attrition rates (e.g. [52,53]), we have allowed for a 30% attrition rate between baseline and pre-assessment, and a further 20% attrition rate between post and follow-up; therefore a total of approximately 120 participants will be required; 60 per group.

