### Study arms

Participants will be randomized to one of two treatment arms: Intervention or wait-list control. Participants from both the intervention and control arms of the study will continue to receive usual care form their regular diabetes clinics throughout the study. Participants in the Intervention arm will receive immediate access to the *NVNG* intervention. Following randomization, participants in the wait-list control arm will be told that they are on a waiting list for 6 months after which time they will be given access to the intervention. During the waiting period they will be sent email or text message reminders to complete their post and follow up questionnaires but will have no other contact with the research team during that time.

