### Randomization procedure

In accordance with CONSORT guidelines [54,55], randomization will occur after participants have completed their baseline questionnaire. A Hypertext Pre-processor (PHP) randomization algorithm method will be used to randomize participants into one of the two study arms. Those who are randomized to the intervention arm will be given immediate access to the online intervention and those randomized to the control arm will be placed on the waiting list and given access to the intervention 6 months after completing the post questionnaire. The CONSORT diagram showing the flow of participants through the study is shown in Figure 1.

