### *NVNG* online parent and adolescent intervention

*NVNG* incorporates two separate but parallel components: an adolescent intervention and a parent intervention. The intervention is designed for parents and adolescents to complete in parallel and is fully self-directed. Adolescents and parents will be provided with individual login details and will work through most sessions separately. However, some activities will be completed collaboratively (e.g., problem solving strategies). Participants will receive weekly email or text message reminders to log in to complete the sessions.

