### Data analysis

Similarity of baseline characteristics of intervention and control participants will be assessed using appropriate summary statistics. Multi-level modeling will be used to compare the outcomes of participation in the intervention and wait-list control arms of the study in terms of pre-/post changes in primary and secondary outcomes while controlling for geographic region, age, gender, and other relevant confounds. Any imbalances in baseline characteristics between the study arms will also be controlled for in the model. Baseline data will be investigated to see if there are any significant factors associated with those participants who drop out in comparison to those that do not, to check for bias. By doing so we will be able to analyze the final results for attrition bias using the predicted probability of attrition as recommended by Heckman [75] and Rubin [76]. An intention to treat analysis and then a longitudinal hierarchical linear model analysis will be conducted, avoiding the need to impute missing data.

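### The attrition check and the drop-out probability built from it name neither trial arm nor 6-week scores, so they are insensitive to selective loss that differs by arm

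*Protocol article*

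**What the plan says.** The Data analysis section of the protocol article describes the attrition step in two sentences. The first reads "Baseline data will be investigated to see if there are any significant factors associated with those participants who drop out in comparison to those that" (the sentence goes on to name the stayers). The second gives its use: "By doing so we will be able to analyze the final results for attrition bias using the predicted probability of attrition". So the section fixes the data (baseline), the contrast (leavers against stayers), the way factors are identified (significance) and the purpose (a probability carried into the analysis of the final results).

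Arm is not mentioned in this step. It does not enter as baseline data either, because under Randomization procedure "randomization will occur after participants have completed their baseline questionnaire". The one comparison by arm in the section concerns everyone at entry: "Similarity of baseline characteristics of intervention and control participants will be assessed using appropriate summary statistics". It is not stated for those who remain.

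On missing data the section adds: "An intention to treat analysis and then a longitudinal hierarchical linear model analysis will be conducted, avoiding the need to impute missing data". Under Sample size calculation the plan allows for 30% loss at a first step and "a further 20% attrition rate between post and follow-up".

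**The concern.** The trial estimates a difference between arms. Loss that is equally selective in both arms changes who is studied but leaves the arms comparable. Loss that differs by arm does not. A contrast of all leavers with all stayers averages over the arms. Selection in one arm is diluted, and selection in opposite directions cancels.

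The document makes arm-specific loss plausible. In the intervention arm there is a self-directed programme to abandon, and "Participants will receive weekly email or text message reminders to log in to complete the sessions". Controls get questionnaire reminders but "will have no other contact with the research team during that time", and they are waiting for access.

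There is also a second step. Those lost between the post and follow-up assessments have reached the 6-week point, where Table 2 schedules both primary measures (CDI-S and RCMAS-S). A baseline-only model sets aside the most recent information on the outcome of interest. Baseline scores may explain part of this later loss, but they need not explain all of it.

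At stake is false reassurance. With loss this heavy, a clean result from the check could be read as showing no attrition bias when it says little about the pattern that matters, and an adjusted analysis using the same probabilities would inherit the gap.

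**Working it through.** **Inputs from Sample size calculation.** 60 per arm; 30% loss, then a further 20%; 64 complete responses required. I take the 30% as loss before the post assessment.

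**The plan's own figures.** Retention is 0.7 × 0.8 = 0.56, so cumulative loss is 44%. Then 64 / 0.56 = 114.3, or 115, which the plan rounds up to about 120. With 120 enrolled, 120 × 0.56 = 67.2 stay and 52.8 leave. The 64 is reproduced by a fixed-effects F test with Cohen's f = .40, 2 numerator degrees of freedom, alpha .05 and 80% power. The document does not state the metric of .40.

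**By hand.** Assume that leavers score 0.5 SD worse than stayers at baseline (an assumption; the document gives no figure), with 44% loss in each arm.

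- Selection in one arm only: that arm's stayers move by 0.44 × 0.5 = 0.22 SD, so the two arms' stayers are 0.22 SD apart at baseline. Over both arms, the leaver–stayer difference is 0.5 / 2 = 0.25 SD. Its standard error is √(1/52.8 + 1/67.2) = 0.184 SD, so z = 0.25 / 0.184 = 1.36 and two-sided power at .05 is about 27%.
- Opposite directions: the leaver–stayer difference over both arms is 0, while the stayers are 2 × 0.22 = 0.44 SD apart.

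**By simulation.** 60 per arm, 44% loss in each arm, one standardised baseline factor driving loss through a logistic model, 4,000 runs per setting. The three values in each cell are for assumed log-odds of 0.5 / 0.8 / 1.0 per SD.

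| Pattern of loss | Baseline gap between the arms' stayers (SD) | Check as worded, % significant | Test within the intervention arm, % | Arm-by-drop-out interaction test, % |
|---|---|---|---|---|
| Same direction in both arms | about 0 | 74 / 98 / 99.7 | 43 / 80 / 92 | 5 / 5 / 5 |
| Intervention arm only | 0.21 / 0.31 / 0.37 | 25 / 48 / 62 | 44 / 79 / 93 | 25 / 48 / 64 |
| Opposite directions | 0.42 / 0.62 / 0.72 | 5 / 4 / 3 | 44 / 80 / 93 | 74 / 98 / 99.8 |

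The check is most sensitive where the arms stay balanced, and no better than chance where they differ most. For loss in one arm the interaction test does no better than the check as worded, so adding another significance test is not the answer. The terms should be kept in the model whatever their p-value.

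**Effect on an attrition-adjusted analysis.** A second simulation used 60 per arm, about 30% then 20% loss, and an assumed within-person correlation of .6. The first loss depended on the baseline score and the second on the 6-week score, differently by arm. Weighting completers' change scores by a baseline-only probability without arm left about 0.06 to 0.17 SD of bias. Weights from a two-step model with arm, arm-by-score terms and 6-week scores left about 0.01 SD or less, with little loss of precision.

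**The case against.** The strongest reply is that the planned longitudinal model already does this work. It contains arm and can use leavers' observed scores. In a simulation with no true effect, the same correlation of .6 and loss driven by observed scores differently by arm, completers differed at baseline by 0.20 to 0.61 SD, yet the likelihood-based estimate of the arm difference in change was biased by less than 0.01 SD at both times. This stands. A reader might infer from the 0.22 and 0.44 SD gaps that the trial's main estimate is biased by that much. The document does not support this: they are baseline gaps among stayers, and no raw comparison of stayers is planned. Nor does it say that the pre-/post comparison drops people without a post form.

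It is also tempting to size these gaps against the planned .40. That fails because the metric is not stated. If it is Cohen's f, it equals d = 0.80 for two equal groups, and 0.22 / 0.80 is about 28%.

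A further reply is that covariates and steps of an attrition model are ordinary content of an analysis plan, which is not shown, and that the participant-flow diagram may already give loss by arm. In part this stands: the article does not say that arm is excluded or that only significant factors enter the probability, and a full plan could add both. But the article does more than stay silent. It specifies the contrast, the data and the purpose, and following that wording gives the insensitive check.

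**Conclusion.** The point holds for the attrition-bias analysis. On the plain reading, the check and the probability derived from it rest on baseline factors found significant between leavers and stayers, without arm or 6-week scores. With 60 per arm and 44% loss, that check flags opposite-direction loss in about 3 to 5% of trials and one-arm loss in about 25 to 62%. Weights built this way can leave about 0.06 to 0.17 SD of bias in a completers' analysis.

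These sizes rest on assumed selection strengths (log-odds 0.5 to 1.0 per SD for the detection rates), equal loss in the two arms and, for the weighting result, a correlation of .6. None of these assumptions is given in the document. The direction of the result does not depend on the exact values: opposite patterns cancel and one-arm patterns are diluted.

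The planned longitudinal estimate is not shown to be biased. If loss depends on scores never observed, neither that model nor the corrected attrition model repairs it.

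**What to change.** Reword the attrition step in the Data analysis section as follows.

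- Model attrition in two steps: baseline to post, and post to follow-up.
- In both steps include arm, baseline CDI-S and RCMAS-S, and arm-by-score terms, kept whatever their p-value.
- In the second step add the 6-week CDI-S and RCMAS-S scores.
- Use the product of the two steps' retention probabilities for follow-up, and the first step's alone for the post assessment, in the attrition-bias analysis already planned.

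The cost is a change of wording before analysis. Trial status says that data collection is still under way, and every variable is already scheduled in Table 2 or known from randomization. The downside is slightly more variable weights.

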**Mediators and moderators**				
Perceived social support	Adolescent satisfaction with support from parents, boyfriend/girlfriend, friends, teachers, employers, diabetes specialists	✓	✓	✓
Other activities	Engagement in employment and extra-curricular activities.	✓		

^Administered to intervention group only.

*Administered to parents and adolescents.

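### A predicted probability of attrition built from baseline data cannot be relied on to show whether the 6-month depression and anxiety results are free of attrition bias, with 44% loss planned for

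*Protocol article*

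**What the plan says.** Under Data analysis, the article describes the attrition step thus: "Baseline data will be investigated to see if there are any significant factors associated with those participants who drop out", compared with those who stay. It then states that "we will be able to analyze the final results for attrition bias using the predicted probability of attrition", with two methodological references. It does not say whether the probability enters as a covariate, a weight or a selection term.

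The outcome model is multi-level, "while controlling for geographic region, age, gender, and other relevant confounds". In addition, "Any imbalances in baseline characteristics between the study arms will also be controlled for in the model". On missing data: "An intention to treat analysis and then a longitudinal hierarchical linear model analysis will be conducted, avoiding the need to impute missing data".

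Under Sample size calculation, "we have allowed for a 30% attrition rate between baseline and pre-assessment, and a further 20% attrition rate between post and follow-up", which takes 64 complete responses up to about 120 participants. I read the first interval as baseline to post-assessment.

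**The concern.** The article names a method and states what it will achieve. The method uses only information available before treatment began. The loss that most threatens a self-directed online programme with a wait-list comparator is different: adolescents in the intervention arm who are not improving may stop logging in and stop responding. That drop-out depends on depression and anxiety after baseline, and a baseline-only probability carries little or no information about it.

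The practical risk is false reassurance. If adding the probability barely changes the treatment effect, a reader will take the result as robust, although the same would happen with a biased one. If a selection term is used instead, the estimate may move or its interval widen for reasons of functional form. The primary outcome is affected, and nearly half of the 6-month data may be missing.

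A lesser issue is the emphasis on significant factors. If significance decides which factors enter the drop-out model, real predictors will often be left out at this sample size.

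**Working it through.** **1. Planned loss, from the article's own figures.**
- Retained at 6 months: 0.70 x 0.80 = 0.56. Lost: 1 - 0.56 = 44%.
- Inflation: 64 / 0.56 = 114.3, so 115 participants. The stated total of about 120 rounds this up.
- With 120 randomised: 120 x 0.56 = 67 completers and 53 leavers.

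**2. What each form of the adjustment can do.**
- *Covariate or weight.* It can account for drop-out explained by the measured baseline factors. A likelihood-based hierarchical model does the same once those factors are in it and adequately modelled.
- *Heckman-type term.* It targets outcome-dependent drop-out, but is well identified only with a strong variable that predicts drop-out and not the outcome. The article names none. Employment and extra-curricular activities are collected at baseline, but Table 2 lists them under mediators and moderators, so the protocol itself links them to outcome.

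**3. Simulations.** The article gives no selection strength, no strength of drop-out predictors and no outcome SD. All three are assumed, with 120 adolescents, about 56% retained and outcome SD about 1. Signs follow the assumed direction of selection, so compare sizes. Pairs are moderate / strong selection. In A to C the unadjusted analysis is the completers' regression.

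| Setting | Unadjusted bias | Probability as covariate | Probability as weight | Two-step term |
|---|---|---|---|---|
| A. Same variables in both models, error correlation 0.6, true effect -0.40 | 0.141 (SD 0.184) | 0.143 (arm not in drop-out model) | 0.143 | 0.077 (SD 0.800) |
| B. One drop-out predictor outside the outcome model and unrelated to outcome (probit slope 0.3); worse-off intervention adolescents leave; true effect 0 | -0.24 / -0.39 (SD 0.19) | -0.24 / -0.39 | -0.25 / -0.41 | -0.25 / -0.38 (SD 0.25 / 0.41) |
| C. As B, but that predictor is related to outcome | not listed | not listed | -0.24 / -0.40 | -0.21 / -0.31 (SD 0.56 / 0.68) |
| D. Likelihood-based longitudinal estimate, worse-off intervention adolescents leave, true effect 0 | -0.14 / -0.24 (SD about 0.20) | -0.14 / -0.24 | not run | -0.15 / -0.26 on completers (SD 0.40 / 0.47) |

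In D without outcome-dependent selection the mean estimate is 0.01, so the model itself is sound. Adding arm and arm-by-baseline terms to the drop-out model gives -0.15 / -0.24. A further check over a wider set of assumed strengths, including a drop-out predictor kept out of the outcome model, had completers' bias of -0.20 to -0.46 SD. It stayed at about -0.20 to -0.58 SD across the three forms.

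With shared predictors at n = 120, the two-step SD ran from 1.2 to about 17 times that of the completers' regression over the assumed range, and its root mean squared error from 1.0 to about 13 times. In A the latter is 0.804 / 0.232 = 3.5.

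**4. Settings where the adjustment works.**
- Two-step at n = 5000, error correlation 0.8: bias 0.351 to 0.003.
- Two-step with three strong predictors (probit slope 0.5 each) outside the outcome model and unrelated to outcome: bias of 0.01-0.18 falls to about 0.03 or less, with root mean squared error 0.8-1.1 times that of the completers' regression.
- Weights using a baseline variable related to outcome but left out of the outcome model, with arm-dependent drop-out: bias 0.333 to 0.055.

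The first needs far more than 67 completers. The second needs variables that the article does not identify. The third is drop-out explained by a baseline factor, which entering that factor in the hierarchical model also addresses.

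**5. Significance as a filter.** For a baseline variable differing by 0.3 SD (assumed) between leavers and stayers: SE = sqrt(1/53 + 1/67) = 0.184; 0.3 / 0.184 = 1.63; power at two-sided 0.05 is about Phi(1.63 - 1.96) = 37%.

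**6. What a delta shift would do.** If 44% of the intervention arm is unobserved and those scores are set 0.40 SD worse, the arm mean moves by about 0.44 x 0.40 = 0.18 SD.

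**The case against.** The strongest reply is that a condensed article may leave the variable list, the form of adjustment and any sensitivity analysis to a fuller document. That stands: their absence is no finding here. It is also fair that the step is described as a check on the results and not as a replacement for the primary estimate, and that every missing-at-random method, including the first part of the fix below, is blind to outcome-dependent drop-out. The point survives because the article goes further and says what the check will deliver.

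A reader might also infer several stronger things that the article does not support:
- *The drop-out predictors are already in the outcome model, so the step is redundant.* The article describes two different sets. One is a search of baseline data generally; the other is region, age, gender, unspecified confounds and arm imbalances. Table 2 holds many baseline measures that could enter only the first.
- *The adjustment cannot move a biased estimate.* It can, as step 4 shows. What fails is reliance on it at this sample size without a strong exclusion variable.
- *The two-step form doubles the error.* No single multiple is right; the ratio depends on the inputs.
- *It is the only protection against attrition.* The hierarchical model protects against missing-at-random drop-out, and reasons for non-completion are collected under Process measures. The probability is the only stated analysis of attrition bias.
- *Non-significant factors will be excluded.* The wording suggests it but does not say so; the 37% applies only if significance is used as a filter.

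**Conclusion.** The point holds in limited form. With 44% loss planned for, a baseline-only predicted probability cannot be relied on to detect or correct drop-out that depends on later depression or anxiety, and an unchanged estimate is not evidence of no attrition bias. As a covariate or weight it adds little once the drop-out predictors are in the hierarchical model. As a two-step term without a strong exclusion variable it can be very imprecise at about 67 completers, with a precision loss from almost none to more than tenfold.

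Under the assumed selection in D, the longitudinal estimate shows a spurious 0.14 to 0.24 SD when the true effect is zero. If the planned 0.40 is a standardised mean difference (the article does not state its metric), that is 0.14 / 0.40 = 35% to 0.24 / 0.40 = 60% of it. These figures show what is possible, not what is expected: nothing in the article fixes the strength or direction of selection.

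**What to change.** In Data analysis:
1. Pre-list the baseline drop-out predictors, enter them in the hierarchical model whether or not they test significant, and call this the missing-at-random analysis.
2. State that this analysis does not test outcome-dependent drop-out, and do not present the predicted-probability result, in any form, as evidence for or against it.
3. Add a delta (tipping-point) sensitivity analysis for CDI-S and RCMAS-S. Shift unobserved intervention-arm scores from 0 to 0.40 SD worse and report the shift at which the conclusion changes, or that it does not change within the range.

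The cost is revised wording and a few extra model runs, with no new data. The article reports that data collection is still under way, so the change can precede the analysis. The downside is that a positive result may be shown to depend on what is assumed about the leavers.
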